
#### Analytic Approach

For preliminary analyses, univariate and bivariate statistics and plots will be used to examine the distributions of and associations between study variables, identify potential multivariate outliers and influential cases, explore patterns of missingness, and check for systematic between-arm differences in baseline participant characteristics. Before addressing the study aims, we will estimate multivariable linear regression models predicting week 8 and week 20 values of each outcome from the main effects of the treatment arm (arm) and the corresponding baseline value of the outcome (baseline) and an arm × baseline interaction term. If the interaction is not significant, an ANCOVA-type approach (described in the following paragraphs) will be used. However, if this interaction is significant, a generalized linear mixed model approach will be used, with repeated measurements of outcomes treated as nested within the participants. Preliminary analyses will inform the choice of link function (eg, natural log) and error distributions (eg, negative binomial) or the transformation of outcome scores used in the primary analyses. R (version 4.1.2) will be used for all analyses and plots.

To assess intervention effects on sleep quality and sleep-related impairment, we will use multivariable linear regression models (following an ANCOVA-type approach), predicting week 8 values on the ISI and secondary sleep outcomes, including the PROMIS Sleep Disturbance questionnaire and Sleep-related Impairment Scale, and sleep efficiency measured via sleep diaries and actigraphy from the study arm (Calm v podcast), adjusting for corresponding baseline values and relevant background covariates (eg, prestudy sleep medication dosage and BMI). These analyses, which will follow a strict intent-to-treat approach, will be supplemented by parallel analyses in which week 8 outcome values will be predicted from dose (minutes of meditation use), with the dose coded as 0 for the podcast arm, while adjusting for baseline outcome measure values and background covariates. These supplemental analyses will address heterogeneity in intervention exposure without including highly collinear arm and dose terms in the same models.

To address the hypotheses regarding the intervention effects on inflammatory markers (TNF-α, IL-6, IL-8, and CRP), fatigue, anxiety, and depressive symptoms, we will estimate models parallel to those estimated for sleep measures, with week 8 outcome values predicted based on the arm, adjusting for corresponding baseline values on outcome measures and relevant background covariates.

To address the hypotheses regarding longer-term intervention effects at week 20, we will use analytic approaches parallel to those to assess differences in change at week 8, with outcomes being predicted from arm or dose (minutes spent meditating), adjusting for corresponding baseline outcome values and background covariates.

To address the hypotheses regarding associations between dose and sustained meditation use (number of weeks with ≥4 days of meditation use) and longer-term change in outcomes within only the Calm intervention arm, we will examine bivariate plots and estimate a variety of multivariable regression models (eg, polynomial linear regression, piecewise linear function, and generalized additive models) to understand the forms of the associations of dose and sustained use and change in outcomes.

If preliminary analyses indicate significant arm × baseline interactions, we will use (instead of an ANCOVA approach) a generalized linear mixed model approach in which a cross-level arm (Calm vs podcast) × time (eg, baseline vs week 8) interaction term is the focal effect for predicting repeated measurements of the outcome measure. This interaction term will capture between-arm differences in changes from baseline to week 8 (or week 20). Differences in change as a function of the intervention dose will be captured using dose × time interaction terms. Although the generalized linear mixed model approach generally does not provide as much statistical power as the ANCOVA approach, generalized linear mixed models (estimated using maximum likelihood) have the advantage of drawing on the strength of all available covariate and outcome data to produce unbiased parameter estimates and SEs in the presence of outcome data that are missing at random.

All preliminary analyses will be supplemented by analyses exploring the interactions between biological sex (male vs female) and the focal effect in each model (eg, sex × arm in ANCOVAs or sex × arm × time in generalized linear mixed models) to determine whether these effects differ by sex. Furthermore, we will conduct sensitivity analyses by examining associations between time of day (eg, proportion of meditation bouts occurring within 2 hours of bedtime) and the proportion of sessions using nonmeditative content and outcomes at 8 and 20 weeks, adjusting for baseline outcome values. As these variables will be highly collinear with the study arm because podcast users will not have any recorded in-app meditation use, sensitivity analyses gauging the potential impact of these variables will parallel the dose-response analyses described previously. Further sensitivity analyses will be conducted to assess the potential impact of (1) changes in the chronic hematological cancer treatment regimen and (2) sleep disorder diagnoses that occur after randomization. For these, analyses of intervention effects will be repeated, excluding data from individuals who experience either of these events, and the results will be compared with those from the full intent-to-treat sample. To maintain the type I error rates at a nominal Cronbach α=.05, we will use *P* values adjusted using the Hommel approach [87].

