#### Primary Outcomes (Sleep)

The primary outcome of changes in sleep disturbance will be assessed using the Insomnia Severity Index (ISI). The ISI, a 7-item measure of reported insomnia symptom severity over the past 2 weeks, has been validated among patients with cancer (Cronbach α=.90) [75]. Total scores range from 0 to 28, with scores of 8 to 14 and ≥15 indicating subclinical and moderate to severe insomnia symptom severity, respectively [75]. An ISI change score >7 is considered a clinically meaningful response to treatment [75]. Sleep will secondarily be assessed using the National Institutes of Health (NIH) Patient-Reported Outcomes Measurement Information System (PROMIS) Sleep Disturbance Short Form 8b, PROMIS Sleep Impairment Scale, actigraphy, and sleep diaries. The PROMIS Sleep Disturbance Short Form 8b comprises 8 items assessing various aspects of sleep on a 1 to 5 Likert scale. The measure generates a total summed score, which is then converted to a standardized *t* score for analysis [76]. The NIH PROMIS Sleep Disturbance Short Form 8b is a reliable and valid measure for assessing sleep disturbance in patients with cancer (Cronbach α=.86) [76]. The PROMIS Sleep-Related Impairment Short Form 8a comprises 8 items assessing various aspects of sleep-related impairment (self-reported perceptions of alertness, sleepiness, and tiredness during usual waking hours and perceived functional impairments during wakefulness associated with sleep problems or impaired alertness) on a 1 to 5 Likert scale. The measure generates a total summed score, which is then converted to a standardized *t* score for use in analyses [77,78]. The PROMIS Sleep-Related Impairment Short Form 8a is a reliable and valid measure for assessing impairments associated with sleep across a range of healthy and patient populations reporting sleep disturbance and sleep impairments (Cronbach α=.85-.91) [77,78].

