### Statistical Analysis

#### Sample Size and Power

All estimates presented here are conservatively based on a generalized linear mixed model analytic approach, in which the focal effect is an arm (Calm vs podcast) × time (baseline vs 8 or 20 weeks) interaction. A generalized linear mixed model approach affords lower power than the preferred analysis of covariance (ANCOVA) approach, which will be pursued if the model’s homogeneity of effect assumption is met (see the *Analytic Approach* section). Assuming a sample SD for ISI scores of 6.0 (derived from the literature on sleep disturbance among patients with cancer [81-85]) and Cronbach α=.05, a complete-case sample size of 28 (n=14 pee arm) would afford a power of 0.80 to detect a clinically meaningful between-arm (Calm vs podcast) differences in ISI scores of >7 points (ie, a standardized between-arm difference of Cohen *d*=1.33). However, anticipated effects on other sleep measures and measures of well-being are generally much more modest; accordingly, the study sample size was determined based on anticipated intervention effects on these outcomes rather than those on the ISI. In our previous work, we found moderate effects of meditation on self-reported psychological well-being (aim 2; Cohen *d*_s_=0.31-0.44), self-reported sleep disturbance assessed via the PROMIS Sleep Disturbance questionnaire (Cohen *d*=0.47), and inflammation biomarkers (Cohen *d*_s_=0.41-0.50) [39]. The meta-analysis by Duong et al [86] suggests somewhat stronger effects of mindfulness (standardized mean difference 0.50) and relaxation (standardized mean difference 0.94) interventions on fatigue. Assuming an effect size typical of those observed across these various outcomes (Cohen *d*=0.45), a conservative estimate of the pre-post correlation for outcome scores (*r*=0.30) and Cronbach α=0.05, a complete-case sample (at 8 weeks) of 220 (n=110 per arm) should afford a power of 0.80 to detect significant between-arm differences in secondary outcomes (and power >0.99 to detect a clinically meaningful difference in ISI scores). Anticipating up to 20% attrition at 8 weeks, we will enroll and randomize 276 participants (n=138 per arm). For aim 3, anticipating up to 30% attrition by week 20 (yielding 194 complete cases; n=97 per arm), tests of intervention effects should have power=0.80 to detect the effects of Cohen *d*≥0.48. Multivariable linear regression analyses of potential dose-response effects on outcomes will take two forms: (1) analysis of all available cases with a dose coded as 0 for the podcast group and (2) analysis using data from the Calm group only. These analyses should have a power of 0.80 to detect small (*r^2^*≥0.039) and moderate (*r^2^*≥0.076) linear dose-response effects.

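### A significance test of arm × baseline decides between ANCOVA and an arm × time mixed model; the switch does not address the interaction and gives up precision

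*Protocol article*

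**What the plan says.** Under Analytic Approach, before any aim is addressed, a regression with arm, baseline and arm × baseline is fitted for every outcome at week 8 and at week 20. The ISI is the primary outcome, so it falls under the rule. The two branches are:

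- "If the interaction is not significant, an ANCOVA-type approach (described in the following paragraphs) will be used";
- "if this interaction is significant, a generalized linear mixed model approach will be used".

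The rule is repeated later in the same section: "If preliminary analyses indicate significant arm × baseline interactions, we will use (instead of an ANCOVA approach) a generalized linear mixed model approach". Sample Size and Power gives the reason: ANCOVA is preferred, provided that its "homogeneity of effect assumption is met".

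The focal term of the fallback is arm × time, described as follows: "This interaction term will capture between-arm differences in changes from baseline to week 8 (or week 20"). No arm × baseline term, and no effect by baseline level, is named in it.

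Both sections say that the mixed model has less power than ANCOVA. The advantage claimed for it is its handling of outcomes missing at random. The Missing Data section already provides multiple imputation for the ANCOVA branch.

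**The concern.** The rule treats a constant treatment effect across baseline as a condition for using ANCOVA. It is not a condition when the target is the average effect in a trial randomised 1:1. The model chosen when the condition fails does not represent the heterogeneity that triggered the choice; it reports one average difference in change, without efficient adjustment for baseline.

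Three things follow:

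- Precision falls when an arm × baseline interaction is detected.
- The primary model for the ISI is unknown until arm and outcome data have been analysed together.
- The 12 named outcomes at two time points may end up under different models, partly by chance.

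**Working it through.** **Inputs.** From Sample Size and Power: d=0.45, pre-post correlation r=0.30, alpha 0.05, 110 complete cases per arm at week 8, ISI SD 6.0. From Enrollment and Randomization: 1:1 allocation. Assumed: a two-sided test, an identity link, equal variances, and no multiplicity adjustment.

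**1. The plan's own figure.** For a difference in change, the SD in outcome-SD units is √(2(1−r)) = √1.40 = 1.183.

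- n per arm = 2 × (1.183/0.45)² × (1.960+0.842)² = 108.5, so 109.
- At 110 per arm, SE = 1.183 × √(2/110) = 0.160. Then 0.45/0.160 = 2.82, and power = Φ(2.82−1.96) = 0.805 (0.802 by noncentral t).

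The stated 110 per arm for 80% power is reproduced. A test of the follow-up score alone needs 78 per arm, and ANCOVA needs 71. The sample size is therefore that of a change-type model.

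**2. ANCOVA on the same inputs.** The SD is √(1−r²) = √0.91 = 0.954.

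- SE = 0.954 × √(2/110) = 0.129. Then 0.45/0.129 = 3.50, and power = Φ(3.50−1.96) = 0.938 (0.936 by noncentral t).
- The variance ratio is 1.40/0.91 = 1.54.
- On the ISI, with SD 6, the 95% half-width is 1.96 × 0.129 × 6 = 1.5 points with ANCOVA and 1.96 × 0.160 × 6 = 1.9 points with the change-type model.

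**3. When the slopes differ by arm.** Let b be the average of the two arms' baseline slopes. With 1:1 allocation, the variance factor is 1−b² for ANCOVA and 2(1−b) for change. The difference is 2(1−b) − (1−b²) = (1−b)², which is never negative. Both methods estimate the same average effect, so the switch cannot gain precision in large samples, whatever the interaction.

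**4. The two-stage rule, simulated at 110 per arm, d=0.45.** The interaction sizes are assumptions; the protocol gives none.

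| Slopes, podcast / Calm | Average slope | Switch fires | Pretest rule | Fixed ANCOVA |
|---|---|---|---|---|
| 0.30 / 0.30 | 0.30 | 5% | 0.93 | 0.93 |
| 0.40 / 0.20 | 0.30 | 34% | 0.89 | 0.935 |
| 0.45 / 0.15 | 0.30 | about 64% | about 0.84 | about 0.93 |
| 0.50 / 0.10 | 0.30 | about 87% | about 0.82 | about 0.93 |
| 0.60 / 0.30 | 0.45 | about 70% | 0.90 to 0.91 | 0.96 |

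Mean estimates were 0.45 under both models in every row, to within simulation error. With no true effect, the pretest rule rejected in 4.6% to 5.5% of trials. ANCOVA that keeps a centred arm × baseline term had power of 0.936 to 0.943 in the runs with average slope 0.30 and unequal slopes.

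**5. Sensitivity.**

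- At r=0.5, power is 0.971 for ANCOVA and 0.916 for change. At r=0.7 it is 0.997 and 0.991.
- Suppose maximum likelihood also uses participants with baseline data only (138 at baseline, 110 completers per arm). The variance per arm is 0.91/110 + 0.49/138 = 0.01182, the SE is √(2 × 0.01182) = 0.154, and mixed-model power rises only to 0.833.

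**6. ISI at the stated 7 points.** The difference is 7/6 = 1.167 SD. Dividing by the SE gives 7.3 for change and 9.1 for ANCOVA, so power is above 0.99 under either.

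**7. Chance switching.** With 12 outcomes and no true interaction, the chance of at least one switch is 1−0.95¹² = 0.46. Over 24 outcome-by-time tests it is 1−0.95²⁴ = 0.71. Both assume a 0.05 pretest and independence; correlation between outcomes would lower them.

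**The case against.** The strongest defence is that the plan has already paid for the weaker branch. The sample size rests on the mixed model, so even near-certain switching leaves about 0.80 at d=0.45 when the average slope is 0.30. The rule has two branches stated in advance, which is not open-ended model choice, and neither bias nor type I error is materially affected. All of this stands. It limits the size of the point but gives no reason for the gate, because the switch does nothing about the interaction.

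A mixed model with baseline means constrained equal across arms would recover ANCOVA's efficiency. The article describes none, and both its sample size and its own statement of lower power fit the unconstrained form.

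Several stronger readings are tempting, but the article does not support them:

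- **That the trial is underpowered, or its ISI test endangered.** The planned 80% survives, and the 7-point ISI target keeps power above 0.99.
- **That power falls to about 0.73.** This needs a podcast slope of 0.30 and a Calm slope of −0.10, an average of 0.10, which departs from the protocol's r=0.30.
- **That benefit will depend on baseline severity.** The article gives no evidence for this or for its size.
- **That the choice is made unblinded.** Allocation is to be withheld from statisticians, and the pretest needs only an arm code. The choice depends on the data but is not shown to be unblinded.
- **That data-driven link functions or transformations and the open covariate list belong to the same defect.** An article commonly leaves these to the analysis plan, which is not shown.

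**Conclusion.** The point holds as one of efficiency and prespecification, and should be fixed. The pretest is unnecessary for a valid average effect, and the model it leads to does not deal with the interaction.

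At the protocol's inputs, an outcome that switches goes from power of about 0.94 to 0.80. Averaged over the rule, the loss is about 9 to 11 points for assumed slope differences of 0.3 to 0.4 SD per SD. It is about 5 points at a difference of 0.2, or where the interaction comes from a steeper control slope (0.60 / 0.30), and under 1 point with no interaction. A higher pre-post correlation shrinks it, and the protocol calls 0.30 conservative.

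The loss bears on ISI effects well below 7 points (d=0.45 is 0.45 × 6 = 2.7 points) and on the secondary outcomes that set the sample size. These figures assume complete cases, an identity link and an unadjusted two-sided 0.05 test.

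**What to change.** - Delete the arm × baseline pretest from Analytic Approach, and the matching condition in Sample Size and Power.
- Name baseline-adjusted ANCOVA, with the multiple imputation already planned, as the primary model for the week 8 ISI and for all other outcomes at both time points, whatever the interaction result.
- Report arm × mean-centred baseline as a supplementary effect-modification analysis. With centring, the arm coefficient is still the average effect.
- Keep the arm × time mixed model as a sensitivity analysis.

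The cost is wording only. The sample size need not change, because it was set for the less efficient model.

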### Enrollment and Randomization

Interested patients with chronic hematological cancer will be directed to complete a web-based eligibility screening questionnaire via REDCap (Research Electronic Data Capture; Vanderbilt University; see Textbox 2 for a detailed list of the eligibility criteria). Ineligible participants will be sent an email notifying them of their ineligibility status and providing resources for patients with cancer, which will include an educational sleep handout and a discount code for Calm. Eligible participants will be sent an email notifying them of their eligibility; asked to review a video-based overview of the study (including the informed consent); and sent a link to electronically sign the informed consent via REDCap, a secure web-based data collection and management platform. Participants will be offered the option of scheduling a call with a member of the research team to review any questions related to the study before providing their consent. Once consent is signed, participants will be (1) asked to complete the baseline questionnaire via REDCap, (2) blindly and randomly assigned to either the Calm intervention or health education podcast control arm, and (3) emailed the study materials (eg, app download instructions, blood draw instructions, and welcome email with important dates and study milestones). As part of the study instructions, all participants will be asked not to participate in any similar interventions, including other meditation apps, medications, or nonpharmacological sleep interventions during the study period. Participants will be blocked or stratified by biological sex and then randomly allocated (with a 1:1 allocation ratio) within the male-female strata to treatments using a pseudorandom number algorithm provided by the study statistician. Research personnel who assign participants to a group will not be the same as those who enroll participants or download and clean data. The group allocation status will be restricted so that statisticians and researchers will remain blind to treatment assignment.

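### Sex is the only stratification factor, but the protocol does not commit to adjusting the main treatment effect for it

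*Protocol article*

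**What the plan says.** **Randomisation.** Enrollment and Randomization states: "Participants will be blocked or stratified by biological sex and then randomly allocated (with a 1:1 allocation ratio) within the male-female strata". No other stratification factor is named.

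**Main sleep models.** Analytic Approach predicts the week 8 value of the ISI and the secondary sleep outcomes from arm, "adjusting for corresponding baseline values and relevant background covariates (eg, prestudy sleep medication dosage and BMI"). The two covariates in brackets are examples. Sex is not among them.

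**Aim 2 and week 20 models.** The inflammatory markers, fatigue, anxiety and depressive symptoms are analysed in the same way, "adjusting for corresponding baseline values on outcome measures and relevant background covariates", with no covariate named. The week 20 models again refer only to background covariates.

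**Fallback mixed model.** If the arm × baseline interaction is significant, an arm × time "interaction term is the focal effect for predicting repeated measurements of the outcome measure". No sex term is mentioned.

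**Where sex appears.** Later in Analytic Approach, supplementary work covers "analyses exploring the interactions between biological sex (male vs female) and the focal effect in each model (eg, sex × arm in ANCOVAs", with sex × arm × time as the mixed-model counterpart.

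**Imputation.** Missing Data builds each imputation model from the variables of the analytic model plus auxiliary variables. Sex is therefore certain to be included only where the analytic model contains it.

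**The concern.** Stratifying on a prognostic factor makes the arms more alike on that factor, so the treatment estimate varies less. A model-based standard error reflects this only if the factor is in the model. Without it, the variation due to sex stays in the residual, the reported standard error is larger than the true one, and the precision gained by stratifying is not reported.

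The supplementary models do not close the gap. A sex × arm term asks whether the effect differs by sex. Once it is in the model, the arm coefficient is the effect at one level of sex (or at a coded midpoint), not the main treatment effect to be reported.

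The protocol gives examples of covariates and describes a separate role for sex. A reader following Analytic Approach could reasonably fit the main models without the one covariate that the design itself calls for. What is at stake is a little precision in each of 12 outcomes: the ISI, two PROMIS sleep scales, sleep efficiency by diary and by actigraphy, four inflammatory markers, fatigue, anxiety and depression.

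**Working it through.** **Inputs from Sample Size and Power.** d = 0.45; pre-post correlation r = 0.30; significance level 0.05 (sidedness not stated, two-sided assumed); 110 complete cases per arm; 20% attrition; 276 randomised. The calculation is "conservatively based on a generalized linear mixed model analytic approach, in which the focal effect is an arm (Calm vs podcast) × time" interaction.

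**Input not in the documents.** R², the share of outcome variance left after baseline adjustment that sex explains. Assumed range: 0 to 0.10.

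**Step 1: the plan's own figure.** The SD of a change score in outcome-SD units is √(2(1 − 0.30)) = 1.183. By the normal approximation, n per arm = 2 × (1.960 + 0.842)² × 1.4 / 0.45² = 108.5, so 109; the noncentral t gives 110. Power at 110 per arm is 0.805 (normal) or 0.802 (t). For attrition, 220 / 0.80 = 275, or 276 with equal arms. The stated sample size reproduces and does not depend on this point.

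**Step 2: ANCOVA without regard to sex.** Residual variance is 1 − 0.30² = 0.91. The standardised effect is 0.45 / √0.91 = 0.472, and the expected test statistic is 0.472 × √(110/2) = 3.498. Power = Φ(3.498 − 1.960) = 0.938.

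**Step 3: stratified allocation, with and without sex in the model.** With exact balance on sex, the true variance of the estimate is (1 − R²) times what a model without sex reports. Hence:

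- ratio of interval widths, without to with sex: 1/√(1 − R²)
- true type I error without sex: 2[1 − Φ(1.960/√(1 − R²))]
- power without sex: Φ((3.498 − 1.960)/√(1 − R²))
- power with sex: Φ(3.498/√(1 − R²) − 1.960)

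| R² (assumed) | Width ratio | Type I error without sex | Power without sex | Power with sex |
|---|---|---|---|---|
| 0 | 1.000 | 0.050 | 0.938 | 0.938 |
| 0.02 | 1.010 | 0.048 | 0.940 | 0.942 |
| 0.05 | 1.026 | 0.044 | 0.943 | 0.948 |
| 0.10 | 1.054 | 0.039 | 0.948 | 0.958 |

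The like-for-like power gain is 0.2, about 0.5 and 1.0 percentage points at R² = 0.02, 0.05 and 0.10.

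**Step 4: simulation check.** This used 220 participants, two equal sex strata, exact balance within strata, 10,000 runs under the null and 4,000 at d = 0.45. At R² = 0, 0.02, 0.05 and 0.10, type I error was 0.048, 0.048, 0.045 and 0.038 without sex, and 0.048, 0.051, 0.051 and 0.050 with it. At R² = 0.10, power was 0.944 without sex and 0.956 with it. This agrees with the formulas to within simulation error.

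The type I figures are per test, before the planned Hommel adjustment. All results in steps 2 to 4 are for the ANCOVA.

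**The case against.** **The list is open.** A reader might infer that the analysis leaves sex out and so ignores the randomisation. The text does not support that. The covariates are introduced as examples, so sex may be among the relevant background covariates, and an analysis plan that is not shown may list it. This part of the objection stands. What remains is that the document names other covariates, gives sex a separate supplementary role, and nowhere commits to it in a main model.

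**Selection on imbalance.** A reader might infer that the preliminary check of between-arm baseline differences will be used to choose covariates, which would make the primary estimate depend on observed imbalance. The document does not say this. Analytic Approach states what the preliminary analyses decide: ANCOVA or mixed model, and link function, error distribution or transformation. Covariate choice is not on that list, and Enrollment and Randomization keeps the statisticians blind to assignment. The point is not made here.

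**The gain is small.** A reader might compare 0.938 (no role for sex) with 0.958 (sex in the model at R² = 0.10) and claim 2.0 percentage points. That is not like for like. If stratification balances sex, the model without sex already benefits, and the gain is 1.0 point at most over the assumed range.

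**The conservatism depends on how allocation is done.** The text says blocked or stratified and gives no block size. If allocation within strata were unrestricted, it would not force balance on sex. Leaving sex out would then not make the standard error too large, and adjusting would be an ordinary gain in precision. This also stands: the conservatism figures assume tight balance and shrink as balance loosens, including through attrition.

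**Conclusion.** The point holds as a small one. The protocol stratifies on biological sex and does not commit to sex as a covariate in any main efficacy model; the supplementary interaction analyses do not fill that role.

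If sex is in fact omitted, the error is on the safe side: the tests are mildly conservative and the intervals somewhat wide, at most by about 5% over the range examined. The treatment estimate is not biased, type I error is not inflated, and 276 randomised remains the right number under the plan's own inputs. ANCOVA power stays near 0.94 or above either way.

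These sizes rest on two assumptions that the documents do not settle: that sex explains 2% to 10% of the residual variance, and that allocation is closely balanced within the sex strata. If sex predicts an outcome hardly at all, adjusting for it changes almost nothing.

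**What to change.** Name biological sex as a fixed covariate in three places in the statistical section:

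- the ANCOVA for every outcome, at week 8 and at week 20;
- the fallback mixed model, where the sex term should be allowed to differ by time, because a term that is constant over time does not bear on the change contrast that is the focal effect;
- the imputation model, so that it matches the analytic model.

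The other background covariates can stay as planned. There is no need to impose one closed covariate list on every outcome, and the supplementary sex-interaction analyses remain as they are.

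The cost is one sentence and, in the ANCOVA, one degree of freedom. Sex is self-reported at baseline and is needed for randomisation, so no new data are required and the sample size does not change.
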